### Data collection

All the participants will be asked to complete two identical scale questionnaires and physical condition examinations before and after the treatment in order to assess their anxiety levels. The first questionnaire and physical condition examination must be completed 30 minutes before the treatment, while the second one will be collected 30 minutes after the treatment.

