### Sample size calculation and statistical analysis

The sample size is estimated, based on changes of Competition State Anxiety Scale (CSAI-2) before and after treatment, from a pilot study. The pilot study was a two-arm design with WAA group and sham acupuncture group. The means of changes of WAA group and sham acupuncture group are 1.9 and −2.0 respectively, while the standard deviations are 6.9 and 5.5. The software Power Analysis and Sample Size (SAS version 9.3, SAS Institute Inc., Cary, NC, USA) was used to perform the sample size calculation. The sample size was calculated with a significance level of 0.05 and power of 0.80. The result was a total required sample size of 86, with 43 for each group. With a maximum dropout tolerance of 15 %, 7 participants are needed for each group. Therefore, 100 participants are needed for the trial, with 50 for each group.

Statistical analysis will be performed using SPSS 15.0 statistics software (SPSS Inc., Chicago, IL, USA) and the statistician is blinded from group allocation. For quantitative data, the distribution pattern and homogeneity of variance will be examined. If there is a symmetric distribution, the mean (M) ± standard deviation will be used for statistical description. A paired samples *t* test will be examined to compare the differences between the quantitative indices before and after treatment in one group, while an independent sample *t* test will be used for comparison between groups. The entire statistical test will use bilateral examination where *P* < 0.05 indicates statistically significant difference.

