### Secondary outcomes

Heart rate, blood pressure, respiratory frequency, tension syndrome curative effect evaluation, and participants’ feeling of acupuncture questionnaire will also be rated.

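### The between-group t test makes no baseline adjustment although CSAI-2 is measured before and after treatment in everyone; ANCOVA would gain precision at almost no cost

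*Protocol article*

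**What the plan says.** Under Sample size calculation and statistical analysis, the protocol article gives two tests for quantitative outcomes. Within a group: "A paired samples *t* test will be examined to compare the differences between the quantitative indices before and after treatment in one group". Between groups: "while an independent sample *t* test will be used for comparison between groups". Neither sentence mentions a covariate, and no baseline adjustment appears elsewhere in the article.

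The Data collection section makes the baseline available for everyone: "All the participants will be asked to complete two identical scale questionnaires and physical condition examinations before and after the treatment". On timing it says: "The first questionnaire and physical condition examination must be completed 30 minutes before the treatment". The second assessment follows 30 minutes after treatment. The secondary outcomes include heart rate, blood pressure and respiratory frequency. The article does not list what the physical examination records, so baseline values for these three are likely but not stated.

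The sample size is "based on changes of Competition State Anxiety Scale (CSAI-2) before and after treatment, from a pilot study". The analysis sentence does not say which variable enters the independent t test. Because planning is on changes, the check below takes the test to be on change scores, the reading most favourable to the plan.

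**The concern.** In a randomized comparison with the same measure before and after treatment, the baseline score usually predicts the post-treatment score. A t test on change subtracts the whole baseline value, which amounts to fixing the regression slope of post on baseline at 1. ANCOVA estimates that slope. When the true slope is below 1, subtraction over-corrects in two ways. It adds variance that ANCOVA avoids, and it leaves an error in the estimate, opposite in sign to any chance baseline difference between the arms. The Randomization and blinding section mentions no stratification by baseline anxiety, so nothing described in the design limits such a difference with 43 to 50 per arm.

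At stake are the width of the confidence interval and how far the single estimate depends on the luck of the allocation. The validity of the test is not in question.

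**Working it through.** **Inputs from the article.** Mean changes 1.9 (WAA) and −2.0 (sham); SDs of change 6.9 and 5.5; two-sided alpha 0.05; power 0.80; 43 evaluable per group. **Assumed, not in the article:** equal pre and post SDs (s), and a common pre-post correlation r, shown as a range.

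**Step 1: reproduce the plan's figure.**
- Difference: 1.9 − (−2.0) = 3.9.
- Pooled SD: √((6.9² + 5.5²)/2) = 6.24.
- Standardized difference: 3.9/6.24 = 0.625.
- The noncentral t calculation gives 42 per group, 84 in total, against the stated 43 and 86. That is within 2 participants.
- At 43 per group: SE = 6.24 × √(2/43) = 1.346, noncentrality 3.9/1.346 = 2.90, 84 df, power 0.817.

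**Step 2: variance under each analysis.**
- Change score: 2s²(1 − r).
- ANCOVA: s²(1 − r²).
- Ratio of ANCOVA to change score: (1 − r²)/(2(1 − r)) = (1 + r)/2.

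**Step 3: power at 43 per group.** The ANCOVA SD is 6.24 × √((1 + r)/2), with 83 df.

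| r | Variance ratio | SD | Power at 43 per group | n per group for 80% |
|---|---|---|---|---|
| change-score t test | 1.00 | 6.24 | 0.817 | 42 |
| 0.3 | 0.65 | 5.03 | 0.944 | 28 |
| 0.5 | 0.75 | 5.40 | 0.911 | 32 |
| 0.7 | 0.85 | 5.75 | 0.874 | 36 |
| 0.8 | 0.90 | 5.92 | 0.855 | 38 |

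The gain over the change-score test runs from 0.855 − 0.817 = 0.038 to 0.944 − 0.817 = 0.127, about 4 to 13 percentage points. The ANCOVA rows charge one degree of freedom for the slope and ignore the further small cost of estimating it.

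**Step 4: effect of a chance imbalance.** Take a baseline difference between arms of one standard error. The baseline SD implied by the change SD is s = 6.24/√(2(1 − r)). The imbalance is s × √(2/43), and the change-score estimate moves by (r − 1) times that imbalance.
- r=0.3: s = 5.27, imbalance 1.14, shift −0.80.
- r=0.5: s = 6.24, imbalance 1.35, shift −0.67.
- r=0.7: s = 8.06, imbalance 1.74, shift −0.52.

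Against the planned difference of 3.9, these shifts are 20%, 17% and 13%. ANCOVA removes this linear dependence on baseline.

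**The case against.** The strongest reply is that nothing here is an error. Under randomization the unadjusted t test is unbiased over repeated allocations and keeps its type I error. On change scores it matches the sample-size basis, already uses the baseline in part, and exceeds its power target. All of this stands, and it limits the point to efficiency and to sensitivity to imbalance in the one trial that is run. The reply does not remove the point. The article names its test outright, so the choice is not one left to an analysis plan, and a better use of data already collected is available.

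Three stronger readings are tempting, and the article does not support them.

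- *The trial is underpowered.* A reader might suppose that the t test is on post-treatment scores and find power of only 0.60 at r=0.7 or 0.44 at r=0.8. That needs a reading the article does not state. It also needs post-score SDs of 6.24/√0.6 = 8.06 and 6.24/√0.4 = 9.87. These are large for a subscale running from 9 to 36, whose greatest possible SD is about (36 − 9)/2 = 13.5. At r=0.9 the implied SD of 13.95 exceeds that limit. These powers should not be relied on.
- *Selecting nervous participants makes regression to the mean a special threat.* Selection is by a symptom questionnaire, with no stated CSAI-2 threshold. Regression caused by selection acts alike on both randomized arms and cancels in their difference. Only the part linked to chance imbalance remains, and that arises in any trial of this form.
- *Vital-sign baselines certainly exist.* The article mentions a physical examination before treatment without listing its contents, so this is an inference.

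**Conclusion.** The point holds as a recommended improvement to a valid analysis. On the article's own planning figures, the change-score t test has power 0.82 at 43 per group. ANCOVA would reduce the variance by 35%, 25%, 15% or 10% at r=0.3, 0.5, 0.7 or 0.8, raising power to about 0.94, 0.91, 0.87 or 0.86. It would also take out a shift of roughly 0.5 to 0.8 points per standard error of baseline imbalance (r from 0.7 down to 0.3).

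These sizes rest on equal pre and post SDs and on an assumed r. The gain shrinks as r rises, and at high r it is small. The direction is more robust. With unequal SDs, the change-score variance exceeds the ANCOVA variance by (1 − slope)² times the baseline variance, so apart from the small cost of estimating the slope, ANCOVA does no worse. The article does not support a claim that the planned test is biased or that the trial as planned lacks power.

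**What to change.** Replace the between-group t test with ANCOVA. For each CSAI-2 score used as the primary outcome, regress the post-treatment value on group and on the baseline value of the same score, and report the adjusted difference with its 95% CI. The Primary outcome section describes three subscales and singles out none, so the wording must say which score or scores it covers. Do the same for heart rate, blood pressure and respiratory frequency where the pre-treatment examination records them. Keep the independent t test on change scores as a sensitivity analysis. This also settles which variable the main comparison uses.

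The cost is a change of wording and one degree of freedom per model, apart from the decision on the score or scores. No new data or participants are needed, and SPSS 15.0, the software already named, can fit the model. The article says that recruitment is still open and the statistician is blinded, so the change can be fixed before unblinding.

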### Primary outcome

#### Competition State Anxiety Scale (CSAI-2)

The CSAI-2 questionnaire is compiled by Martens et al. [21] on the theory of multidimensional competition state anxiety. The revision of CSAI-2 was re-corrected by ZhuBeili (1994) [22]. The scale is composed of 3 subscales: each subscale score, respectively, has 9 items. Scores are from 9 to 36, the higher the score means the higher the cognitive state anxiety, the somatic state anxiety and the state self-confidence. It is the primary outcome to assess competitive anxiety and the efficacy of treatment.

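### The primary outcome is the whole CSAI-2, described only as three subscales of mixed direction, while the sample size rests on one unnamed CSAI-2 change, so the stated alpha and power attach to no identified score.

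*Protocol article*

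**What the plan says.** **Primary outcome.** Under the heading Competition State Anxiety Scale (CSAI-2), the protocol article describes the instrument in two steps: "The scale is composed of 3 subscales: each subscale score, respectively, has 9 items", and then, for scores of 9 to 36, "the higher the score means the higher the cognitive state anxiety, the somatic state anxiety and the state self-confidence". Of the instrument as a whole it says: "It is the primary outcome to assess competitive anxiety and the efficacy of treatment". It describes no total score, reverse-scoring or composite, and puts no subscale first.

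**Sample size.** Under Sample size calculation and statistical analysis, the calculation is "based on changes of Competition State Anxiety Scale (CSAI-2) before and after treatment, from a pilot study". One pair of means is given: "The means of changes of WAA group and sham acupuncture group are 1.9 and −2.0 respectively". For spread, "the standard deviations are 6.9 and 5.5". Significance level 0.05 and power 0.80 lead to 43 per group, raised to 50 for dropout. The article does not say which CSAI-2 score these figures describe, or whether change means after minus before or the reverse.

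**Testing.** The same section compares groups on quantitative measures with an independent-samples t test. On thresholds, "The entire statistical test will use bilateral examination" at P < 0.05. It sets no order among tests and does not divide alpha.

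**The concern.** A significance level and a power figure describe one test of one variable. Here the variable is not identified in either place where it should be. The outcome section offers three candidate scores, and the sample-size section uses one score without naming it.

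The pilot means do not settle the matter. Read as after minus before on an anxiety subscale, +1.9 with WAA and −2.0 with sham would mean that anxiety rose with WAA and fell with sham. The figures favour WAA in two cases: before-minus-after change on an anxiety subscale, or after-minus-before change on self-confidence. These are different endpoints, and the article says that the trial is about precompetition anxiety.

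At stake is what a positive result would mean. As written, the choice of score could be made after the results are known. A significant difference on self-confidence alone could then be reported as the primary result of an anxiety trial, and the quoted 80% power might belong to a score other than the one reported.

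**Working it through.** **Inputs** (sample-size section): mean changes 1.9 and −2.0; SDs 6.9 and 5.5; two-sided alpha 0.05; power 0.80; 1:1 allocation; 43 per group.

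**1. Reproduce the plan's figure.**
- Difference: 1.9 − (−2.0) = 3.9.
- SD: √((6.9² + 5.5²)/2) = √((47.61 + 30.25)/2) = √38.93 = 6.24.
- Standardised difference: 3.9/6.24 = 0.625.
- Normal approximation: n = 2(1.960 + 0.842)²/0.625² = 40.2, so 41 per group.
- Exact noncentral t: 41 per group gives 79.8% and 42 gives 80.8%, so 42 per group. Allowing for unequal variances also gives 42.
- Power at the stated 43: 81.7% (exact t).

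A one-sided test would need 32 by the normal approximation, so the calculation is two-sided. The stated 43 is sound for **one** comparison at an undivided 0.05.

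**2. How many scores are described?** A range of 9 to 36 fits a 9-item subscale. Three such subscales would sum to 3 × 9 = 27 up to 3 × 36 = 108. The stated range is therefore a subscale range, and only subscale scores are described.

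**3. What follows under each success rule?** The article states no rule, so each case below is conditional.

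*Any one subscale suffices, each tested at 0.05.* If independent, family-wise error = 1 − 0.95³ = 0.143. For correlated subscales (simulation of three equally correlated normal statistics; correlations assumed, since the article gives none):

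| Correlation | Family-wise error |
|---|---|
| 0 | 14.3% |
| 0.3 | 13.6% |
| 0.5 | 12.5% |
| 0.7 | 10.9% |
| 0.9 | 8.4% |

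*All three must succeed, each at 0.05.* The error rate stays at or below 5%. With the pilot effect on every subscale and independence, power is 0.817³ = 0.546, about 55%. In simulation it rises with correlation to about 75% at 0.9, still below 80%.

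*One named score.* Alpha of 0.05 stands, and 43 per group stands if the pilot figures belong to that score.

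**4. If all three stay primary with adjustment.**
- Bonferroni: 0.05/3 = 0.0167. Per-subscale power is 67.5% at 43 per group and 75.3% at 50 with no dropout; 80% needs 56 evaluable per group.
- Holm rejects at least as often as Bonferroni. Simulated at 43 per group with an effect of 0.625 on all three subscales and correlations from 0 to 0.9, it gives about 73% to 77% average power per subscale, and about 77% to 97% for at least one subscale.
- Holm falls back to about 67% only when a single subscale responds.

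**The case against.** **No sentence says that each subscale is a separate primary test.** This is correct. The outcome section speaks of the primary outcome in the singular, and P < 0.05 is a general threshold. A reader might infer that the plan carries a type I error of up to 14%. The article does not support that as a flat statement: it needs an any-subscale success rule, which is not written, and correlations that are not given. Separate testing is the natural reading, because only subscale scores are described and one threshold covers all tests, but it remains a reading.

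**Multiplicity procedures and scoring details may be left to an analysis plan or to the cited scale.** This stands for the procedure. It does not excuse the choice of primary score or the identity of the score behind the sample size. The article gives a full primary-outcome section and full sample-size inputs, and leaves both ambiguous.

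**A total score may have been meant.** A reader might infer that the trial will add the three subscales and so cancel its own effect. No sum is described anywhere. An unreversed sum would mix opposite directions: with equal favourable shifts it would keep 1 of 3 raw points. That says less about detectability, because the variance of the sum also shrinks if self-confidence runs opposite to anxiety.

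**The sign of the pilot means is harmless.** Before minus after is an ordinary convention, and the sign does not alter a two-sided sample size. Both points stand. A reader should not infer that the pilot showed WAA to raise anxiety. What remains is that the sign cannot identify the score.

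**Conclusion.** The point holds as a defect in the definition of the endpoint. The sample-size arithmetic is not at fault: 43 per group reproduces to within two participants. But it covers one score, the article does not say which, and the primary outcome as described contains three scores that do not all run the same way.

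The consequence depends on a success rule that the article leaves open. If any one subscale at 0.05 suffices, family-wise error is about 8% to 14% for assumed correlations from 0.9 to 0. If all three must succeed, alpha is protected but power is below 80% (about 55% if the subscales are independent and share the pilot effect). If a total is meant, it is undefined. Only a single named score that is also the source of the pilot figures makes the stated 0.05 and 80% correct.

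This should be corrected before unblinding, because it determines what a positive trial can claim.

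**What to change.** 1. Name as the single primary endpoint the between-group difference in change on the CSAI-2 subscale that produced the pilot figures, and confirm that it is an anxiety subscale, since anxiety is the trial's question.
2. State the direction of change and relabel 1.9 and −2.0 with the subscale name and matching sign.
3. Make the other two subscales secondary, and do not use an unreversed sum of the three.
4. If the pilot figures came from another score, such as self-confidence, restate the power for the endpoint that is named.
5. If all three subscales are to stay primary, adopt a multiplicity procedure such as Holm and restate the power, saying whether it means per-subscale power or power for at least one, and under which effects and correlations. The figure of about 67% at 43 per group is Bonferroni per-subscale power and should not be quoted for Holm in general.

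**Cost.** Items 1 to 3 change wording only, with no added participants, and the Trial status section reports that recruitment is still under way. The downside is that two of the three subscales can no longer make the trial positive on their own. Item 4 may show lower power than stated. Item 5 means either accepting that or enlarging the trial; under Bonferroni, 80% per subscale needs 56 evaluable per group against the planned 43.

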### Secondary outcomes

Heart rate, blood pressure, respiratory frequency, tension syndrome curative effect evaluation, and participants’ feeling of acupuncture questionnaire will also be rated.

### Data and safety monitoring

The data will be collected by a well-trained assessor to improve data quality and regular monitoring will be conducted for quality control by a researcher. The assessment of safety will primarily be based on the frequency of adverse events (AEs). AEs will be defined as any unfavorable signs or symptoms temporally associated with WAA treatment, such as subcutaneous bleeding, fainting, heart palpitations, dizziness during acupuncture treatment. The severity and causality of AEs will be immediately recorded in the case report form by the researcher, who will report the AE to the primary investigator and ethics committee. Then, the decision will be made on whether the patient needs to withdraw from the trial. If any AEs occur, the appropriate treatment will be immediately provided to the participant.

## Discussion

To our knowledge, the use of the common filiform needle in acupuncture intervention is difficult to incorporate into a blind trial because of the special intervention procedure. According to traditional acupuncture theory, filiform needle therapy to the acupoints always gives the participants the sensation of obtaining *qi* (eg. sourness, numbness, distention and pain). An acupuncture trial design without requesting whether *qi* is obtained by the participants could not reflect the correct and real therapeutic effect of acupuncture [23]. However, for WAA, needling sensation is not required. It is innovative that we could design a randomized controlled single-blind trial with a non-penetrating sham WAA group. In the trial, the subjects were asked to wear an eye mask. Under this condition, they did not know which intervention they would be given and also could not distinguish therapuetic intervention in the subsequent treatment. The participants’ feeling of acupuncture questionnaire would be arranged at the end of treatment in order to exclude the breaking of blinded subjects. Therefore, we believe that this method can serve as an effective placebo intervention and that this study will be able to provide high-quality evidence for the efficacy of WAA for precompetition nervous syndrome.

The trial also has a limitation. The degree to which precompetition nervous syndrome is experienced is closely related to the championship level at which sport is played. Hence, higher levels of competition will cause more precompetition anxiety. Therefore, the trial may be more easily performed at this level as it will provide a greater number of participants. In this study, we could not have conducted the trial in large national sporting events due to the limits imposed by those conditions. Thus, the trial will only reflect the treatment effects in certain circumstances, but hopefully the results will yield important information to provide help and useful advice to the athletes in national athletic meetings or at future Olympic Games.

## Trial status

Participants are currently being recruited into the study. The study will be finished on 30 September 2015.

### Consent

Written informed consent was obtained from the patient for publication of this manuscript and accompanying the image in Fig. 2. A copy of the written consent is available for review by the editor-in-chief of this journal.

## Abbreviations

AEs: Adverse events
CONSORT: Consolidated standards of reporting trials
CSAI-2: Competition state anxiety scale
M: Mean
STRICTA: Standards for reporting interventions in clinical trials of acupuncture
WAA: Wrist-ankle acupuncture
